# Associations between primary motor cortex organization, motor control and sensory tests during the clinical course of low back pain. A protocol for a cross-sectional and longitudinal case-control study

**DOI:** 10.1016/j.conctc.2022.101022

**Published:** 2022-11-03

**Keywords:** Low back pain, Transcranial magnetic stimulation, Cortical organization, Motor control, Sensory tests, CoG, Center of Gravity, CPM, Conditioned Pain Modulation, EMG, Electromyography, LBP, Low Back Pain, M1, primary motor cortex, MEP, Motor Evoked Potential, MRI, Magnetic Resonance Imaging, MVC, Maximum Voluntary Contraction, PPT, Pressure Pain Threshold, TMS, Transcranial Magnetic Stimulation, QST, Quantitative Sensory Testing

## Abstract

**Background:**

In people with low back pain (LBP), altered motor control has been related to reorganization of the primary motor cortex (M1). Sensory impairments in LBP have also been suggested to be associated with reorganization of M1. Little is known about reorganization of M1 over time in people with LBP, and whether it relates to changes in motor control and sensory impairments and recovery. This study aims to investigate 1) differences in organization of M1 of trunk muscles between people with and without LBP, and whether the organization of M1 relates to motor control and sensory impairments (cross-sectional component) and 2) reorganization of M1 over time and its relation with changes in motor control and sensory impairments and experienced recovery (longitudinal component).

**Methods:**

A case-control study with a cross-sectional and five-week longitudinal component is conducted in participants with LBP (N = 25) and participants without LBP (N = 25). Participants with LBP received usual care physiotherapy. Various tests were administered at baseline and follow-up. Following an anatomical MRI, organization of M1 (Center of Gravity and Area of the cortical representation of trunk muscles) was determined using transcranial magnetic stimulation. Quantitative sensory testing, a spiral-tracking motor control test, graphesthesia, two-point discrimination threshold and various self-reported questionnaires were also assessed. Multivariate multilevel analysis will be used for statistical analysis.

**Conclusion:**

We will address the gaps in knowledge about the association between reorganization of M1 and motor control and sensory tests during the clinical course of LBP. This study is registered at DOI 10.17605/OSF.IO/5C8ZG.

## Introduction

1

Motor control of trunk muscles is altered in people with low back pain (LBP) [[1], [2], [3], [4], [5]]. Altered trunk motor control in LBP has been related to the (re)organization of the primary motor cortex (M1) [[6], [7], [8]]. Regarding the reorganization of M1 of trunk muscles, a lower level of intracortical inhibition of the lumbar multifidus muscle [9] and a smaller map volume [10] have been observed in people with LBP compared to people without LBP. Furthermore, a relation between map volume and the severity of LBP has been demonstrated [11,12].

To determine the cortical representation, as a measure of cortical reorganization, the location of the Center of Gravity (CoG; the amplitude weighted center of cortical representation of a muscle) and area can be analyzed. The CoG is a valid outcome for measuring this representation [13,14].

There is conflicting evidence regarding the altered location of the CoG of the erector spinae in people with LBP: both a more posterior [10] and a more anterior [11,12] location have been found compared to people without LBP. Additionally, in people with LBP, an increased overlap in the cortical representation of the erector spinae and deep multifidus muscle [10] has been revealed.

Changes over time in the organization of M1 have been shown in people with LBP regarding: increased intracortical inhibition after isometric deep multifidi training [8]; increased intracortical facilitation after repetitive peripheral magnetic stimulation [15]; increased map volume and increased discrete peaks after combined transcranial direct current stimulation and peripheral electrical stimulation compared to a reduced map volume following peripheral electrical stimulation alone, and no difference in the amount of peaks following either one of the stimulations separately [16]. A prospective cohort study revealed an association between a smaller map volume of M1 in the acute stage of LBP with a higher pain intensity at 6-month follow-up. However, after adjustment for confounding predisposing factors, such as blood biomarkers for inflammation, psychological variables (emotional and cognitive pain experience) and mechanical pain sensitization, this association was no longer significant [17].

Little is known about changes of the CoG of trunk muscles over time in people with LBP, and how this relates to recovery. A proof-of-principle study revealed an anterior and medial shift of the CoG of the transversus abdominis muscle following exercises of contraction of this muscle, whereas in the control intervention of self-paced walking no changes were observed [7]. In addition, a prospective cohort study revealed that a smaller L3 map volume was a predictor for LBP at 6-months follow-up, in contrast to the CoG which revealed not to be a predictor [18].

Sensory impairments are also suggested to be associated with reorganization of M1 [3,19]. Adaptive motor behavior in people with LBP may lead to selective muscle activation and kinematics. This will lead to a change in sensory feedback from the lumbar area. This, in turn, might contribute to neuroplastic changes in the motor and sensor cortex and to proprioceptive impairments reducing the ability to control lumbar movement [3]. This suggested relation has hardly been studied, and has not yet been demonstrated [12].

Because of the scarce and inconsistent evidence, there is a need for a better understanding of the relations between motor control changes, sensory changes, and M1 reorganization of trunk muscles in people with LBP. To investigate this relation, we will conduct a case-control study with both a cross-sectional and longitudinal component. The aim of the cross-sectional part is to investigate differences between people with LBP and without LBP regarding the reorganization of M1 of trunk muscles, and the performance on motor control and sensory tests. In addition, the association between the organization of M1 and the performance on motor control and sensory tests will be studied. The aim of the longitudinal part is to analyze reorganization of M1 of trunk muscles as well as changes in motor control and sensory test performance over time, within and between people with LBP (recovered and non-recovered) and without LBP. In addition, the associations between reorganization of M1, and changes in motor control and sensory test performance over time, and between groups, will be studied.

## Methods

2

### Study design

2.1

A case-control study with a cross-sectional component and five-week longitudinal component was conducted in participants with and without LBP. All participants provided written informed consent before participating in the trial. The study has been approved by the Medical Ethics Committee Brabant, number NL70934.028.19/P1944. The study is registered in the Open Science Framework (10.17605/OSF.IO/5C8ZG). The STROBE checklist for reporting observational studies has been followed.

### Participants

2.2

We included people with LBP (>24 h) [20] who were seeking medical or physiotherapy care, who either had chronic LBP (pain duration of >12 weeks) and had recently experienced a flare up, or people with recurrent LBP. LBP was defined as pain between the lower rib margins and the buttock creases [21]. A flare up was defined as an increase in pain of at least two points in pain intensity on a 0–10 Numeric Pain Rating Scale and also an increase in the impact of LBP on usual activity [22]. Recurrent LBP was defined as an episode of LBP lasting >24 h, separated by a pain-free period of more than one month without LBP [23], and where LBP had an impact on usual activity. With these selection criteria, we aimed to include people who were anticipated to experience fluctuations or recovery in pain and function. The following exclusion criteria were used: major spinal pathology, a history of lumbar radiculopathy or spinal operation, circulatory diseases, or pregnancy and the six-month postpartum period, younger than 18 or older than 65 years of age, or not meeting the safety criteria for Magnetic Resonance Imaging (MRI) or Transcranial Magnetic Stimulation (TMS) [24]. People without LBP had to be free of an episode of LBP in the preceding three years and were matched for sex and age to the people with LBP. People with LBP were recruited from five primary care physiotherapy clinics in The Netherlands. People without LBP were recruited from the acquaintances, friends, or relatives of the patients.

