### Procedure

2.3

All participants were measured twice with an interval of five weeks (± one week), since a marked improvement is expected in the first six weeks of a LBP episode [25]. During this five-week interval, the participants with LBP received usual care in a primary care physiotherapy clinic. The therapists of these clinics received information about possible exercises for motor control and sensory accuracy, but were free in their choice of therapy form, duration, and intensity. However, during therapy they were not allowed to use the tests of which the results served as outcomes in the present study. All participants first underwent a T1 weighted MRI of the brain, after which they completed self-reported questionnaires, performed quantitative sensory tests, a motor control test, sensory tests and underwent TMS to determine the organization of M1. The MRI was only conducted before the first measurement. Below, each of these assessments is described in detail. See Fig. 1 for a flowchart of the study.

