#### Questionnaires

2.4.1

All participants completed a questionnaire regarding demographic variables. Participants with LBP also completed 1) a general questionnaire containing questions on location and duration of their pain; 2) a Numeric Pain Rating Scale (0–10); 3) the Oswestry Disability Index; 4) the Pain Anxiety Symptom Scale; and 5) the Central Sensitization Inventory. All questionnaires have adequate reliability and validity [[26], [27], [28], [29], [30]]. At 5-week follow-up, participants with LBP indicated their overall level of recovery on a Global Perceived Effect scale (GPE-Dutch Version, 7-point Likert scale) and completed the Numeric Pain Rating Scale, Oswestry Disability Index, Pain Anxiety Symptom Scale and Central Sensitization Inventory. Participants without LBP reported whether they were still free of LBP.

For our analyses, we are interested in those participants with LBP who showed recovery, versus those who did not. These groups (recovered and non-recovered LBP participants) are defined based on their ‘Global Perceived Effect’ after 5 weeks. The LBP participants is asked how much their back condition has improved or deteriorated on a 7-point Likert scale. Category 1 (‘completely recovered’) and category 2 (‘much improved’) will be considered as recovered. Category 3 (‘slightly improved’), 4 (‘equal’) and 5 (‘slightly deteriorated’) will be considered as ‘unchanged’, category 6 (‘much deteriorated’) and 7 (‘completely deteriorated’) as deteriorated. Therefore, category 3 till 7 will be considered as non-recovered [31].

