### Statistical analysis

2.6

Missing data will be addressed according the STROBE statement [47]. When data are missing <5% per variable per case, complete case analyses will be performed. The type of missing data will be first checked and reported. When necessary, multiple imputation will be performed before analysis.

To analyze cross-sectional differences between participants with and without LBP regarding the organization of M1 of trunk muscles and the performance on motor control and sensory tests, multivariate mixed model analyses will be used, with a 2-level structure. Regarding the organization of M1 of trunk muscles, the MEPs (i.e., longissimus at level L3 and L5, internal and external abdominal oblique muscles) are clustered within the participant. Regarding the motor control and sensory tests, the test scores are clustered within the participant. The same analyses will be used to analyze the association between the organization of M1 of trunk muscles and the performance on a motor control and sensory tests. For the latter, the organization of M1 of trunk muscles will be used as outcome.

To analyze changes over time in organization of M1 of trunk muscles and to analyze differences in changes over time between participants with LBP (recovered and non-recovered) and participants without LBP, multivariate mixed model analyses with a 3-level structure will be used. The MEPs are clustered within the repeated measurements and the repeated measurements are clustered within the participant. The same analytical procedure will be followed to analyze the differences in changes over time in performance on motor control and sensory tests between participants with LBP (recovered and non-recovered) and participants without LBP. In these multivariate mixed model analyses, time, group and the interaction between time and group will be added.

Finally, the longitudinal associations between organization of M1, and the motor control and sensory tests performance over time, will be analyzed with multivariate mixed model analyses. For the latter, again, the organization of M1 of trunk muscles will be used as outcome.

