This study has some limitations. We defined the selection criteria in such a way that we anticipated a proportion of the participants to recover after five weeks. We therefore did not want to solely recruit people with persistent pain, but opted to include people with a fluctuating pain trajectory. However, it is possible that either the number of recovered or the number of non-recovered LBP participants will be small. This may influence the power of the statistical analysis. However, in general the power of longitudinal analyses is higher than the power of cross-sectional analyses, because of the gain in the number of observations. Despite some loss because of the partly correlated observations, more observations will remain for the analysis than in a cross-sectional design. Based on the sample size calculation, for the comparison between participants with LBP and participants without LBP of cortical reorganization over time, the power is therefore expected to be sufficient.

Although people with longer lasting symptoms might be more prone to reorganization of M1, we decided to include participants with a pain duration >24 h [20] who were seeking medical or physiotherapy care, since a marked improvement is expected in the first six weeks of a LBP episode [25].

In this study we used 100% of the maximum stimulator output, as 120% of the motor threshold of the longissimus muscle generally exceeds the maximum output of the stimulator [9,10]. Therefore, no individual stimulation intensity was used. Subsequently, for some participants the stimulation intensity could be too high for accurate determination of the area [43] and for others too low for inducing MEPs.

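### The recovered versus non-recovered contrast in M1 may be confounded by type or duration of LBP, and the stated longitudinal terms cannot separate the two

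*Protocol article*

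**What the plan says.** **Entry (2.2 Participants).** The LBP group takes people "who either had chronic LBP (pain duration of >12 weeks) and had recently experienced a flare up, or people with recurrent LBP". The recurrent route has a lower limit only: "Recurrent LBP was defined as an episode of LBP lasting >24 h", after a pain-free period of more than a month. For the chronic route, the flare must be recent, but no number of days or weeks is given. Controls "were matched for sex and age to the people with LBP"; that matching does nothing to balance recovered against non-recovered participants.

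**Follow-up interval (2.3 Procedure).** Five weeks was chosen "since a marked improvement is expected in the first six weeks of a LBP episode". The Discussion repeats this reason.

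**Recovery grouping (2.4.1 Questionnaires).** Groups are formed from the Global Perceived Effect scale at follow-up. Categories 1 and 2 count as recovered. "Therefore, category 3 till 7 will be considered as non-recovered". The same section says that LBP participants complete "a general questionnaire containing questions on location and duration of their pain".

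**Model (2.6 Statistical analysis).** For changes over time in recovered, non-recovered and control participants: "In these multivariate mixed model analyses, time, group and the interaction between time and group will be added". The article names no adjustment, stratification or sensitivity analysis for LBP type or duration.

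**Discussion.** The authors accept that "people with longer lasting symptoms might be more prone to reorganization of M1", but raise this only when explaining whom they enrolled.

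**The concern.** Recovery status is not assigned. It is observed five weeks after baseline in a group that is mixed by design. Someone a few days into a recurrent episode, someone ten weeks into one, and someone with years of pain and a recent flare all enter the same LBP group. Entry is not tied to the onset of the episode or flare, although the interval was chosen for what happens early in an episode.

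Confounding needs a factor linked both to the grouping and to the outcome. The article suggests both links: timing within the episode to improvement, and longer symptoms to M1 reorganization. Neither is carried into the analysis.

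A stated longitudinal aim is to compare M1 reorganization between recovered and non-recovered participants. If the two groups differ in chronicity, a difference in M1 could be read as a marker of recovery when it marks the kind of LBP, or a real relation with recovery could be masked. The Introduction cites a cohort in which an association between M1 map volume and later pain lost significance after adjustment. The adjustment factors there were other ones, but it shows that such associations can be sensitive to adjustment.

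**Working it through.** **1. The plan's own figure.** Section 2.5 gives means of 1.4 and 0.8 (difference 0.6), pooled SD 0.68, α 0.05 (two-sided assumed) and power 0.80.

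n per group = 2 × (1.96 + 0.8416)² × 0.68² / 0.6² = 20.2, rounded up to 21.

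This reproduces the stated 21 (22 with the t distribution). For dropout, 21 / 0.85 = 24.7, so 25; at 20%, 21 / 0.80 = 26.25, so 27. The figure concerns LBP versus no LBP. It is used below only to supply a scale (0.6 and 0.68).

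**2. Formula for the contrast in M1 level.** With no true relation to recovery:

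spurious difference = (share recurrent among recovered − share recurrent among non-recovered) × (M1 difference between LBP types).

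**3. Assumed inputs.** The documents give neither the mix of types, nor recovery by type, nor the M1 difference between types. Assume 12 chronic and 13 recurrent participants, with recovery in 30% and 70% respectively.

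- Recovered: 13 × 0.7 = 9.1 recurrent and 12 × 0.3 = 3.6 chronic; 9.1 / 12.7 = 71.7% recurrent.
- Non-recovered: 3.9 recurrent and 8.4 chronic; 3.9 / 12.3 = 31.7% recurrent.
- Difference in share: 0.40.

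Recovery of 40% and 60% gives a difference in share of 0.20; recovery of 20% and 80% gives 0.60.

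**4. Illustration for M1 level (in SD of 0.68).**

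| Difference in share | Type effect 0 | Type effect 0.3 | Type effect 0.6 |
|---|---|---|---|
| 0.20 | 0 | 0.06 (0.09 SD) | 0.12 (0.18 SD) |
| 0.40 | 0 | 0.12 (0.18 SD) | 0.24 (0.35 SD) |
| 0.60 | 0 | 0.18 (0.26 SD) | 0.36 (0.53 SD) |

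In a simple comparison of 12 with 13 participants, the false-positive rate stays at 0.05 with no type effect. At a type effect of 0.6 it rises to 0.071, 0.135 and 0.245 for the three rows.

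**5. The time-by-group term.** Each person is measured twice. A type difference that is the same at both visits drops out of within-person change, so none of the figures in step 4 carries over. The formula becomes:

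spurious difference in change = (difference in share) × (difference between types in mean five-week change).

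With a difference in share of 0.40, the bias is 0.40 of whatever that difference in change is. The documents give no value for it. It is plausible that it is not zero, because the reason given for the interval implies that people nearer the start of an episode improve more over the five weeks. That statement, however, concerns clinical improvement, not M1.

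**6. Price of adjustment.** Adding a binary type covariate multiplies the variance of the recovery contrast by about 1 / (1 − r²), with r approximated by the difference in share. Power is for a level difference of 0.6 (SD 0.68) at 12 versus 13, and is 0.56 unadjusted.

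| r | Variance factor | Power after adjustment |
|---|---|---|
| 0.20 | 1.04 | 0.54 |
| 0.40 | 1.19 | 0.49 |
| 0.60 | 1.56 | 0.39 |

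**The case against.** **The size belongs to a different term.** The longitudinal question is answered mainly by time by group, and a stable difference between types cancels there. This stands. A reader might take 0.35 SD as the bias in the main longitudinal test; step 5 shows that it is not.

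**The inputs are not in the documents.** The value 0.6 is the whole planning difference between people with and without LBP, used here as an upper value for a difference between two kinds of LBP. Nothing supports it as an estimate, and at zero the bias vanishes. This stands too, which is why the illustration starts at 0.

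**Possibility is not fact.** A reader might infer that the results are confounded, or that the recovered group will consist mainly of recent recurrent cases. The documents do not say so. Section 2.2 chose both entry routes to find people expected to fluctuate or recover, no statement says that chronic LBP in flare recovers less often than recurrent LBP, and the Discussion says only that longer symptoms might matter.

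**A fuller plan may list covariates.** Section 2.6 does not say that no other term will enter, and an article condenses. This has some weight. But the point does not rest on silence: the article states the longitudinal terms, and those terms leave out a factor that the authors themselves connect with M1.

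**Adjustment changes the question.** The aims speak of a relation with recovery, and a model adjusted for type asks about recovery at a given type. That is a reason to report both results. In addition, LBP type and duration are undefined for controls, so such a covariate cannot simply be put into the three-group model. This limits the fix.

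**Conclusion.** The point holds in a limited form. The article pools two kinds of LBP with widely varying duration, suggests that timing bears on recovery and duration on M1, and names longitudinal terms that contain neither. Run as written, the recovered versus non-recovered contrast cannot tell recovery from chronicity, so it may be confounded.

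Size and direction cannot be derived from the documents. For M1 level, the illustration gives 0 to 0.24 (0 to 0.35 SD) at a difference in share of 0.40, and at most 0.36 (0.53 SD) at 0.60. It rests on an assumed 12/13 mix, assumed recovery rates, and a between-type effect anywhere from 0 to 0.6. For time by group there is no figure, and bias arises only if change differs by type or duration.

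The deliberate breadth of entry is not at fault, and neither the sample size calculation nor the planned three-group model is shown to be wrong. What needs changing is how a recovery difference is analysed and interpreted.

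**What to change.** In section 2.6, before the data are analysed:

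1. Keep the planned three-group model.
2. Add a pre-specified model restricted to LBP participants. It contrasts recovered with non-recovered and contains time, recovery group, time by recovery group, LBP type (chronic with flare or recurrent) and time by LBP type. Fix type as the single covariate now, so that the choice among type, episode duration and pain duration is not left open.
3. Report this model beside the unadjusted result, and tabulate recovery by LBP type and by pain duration.
4. State that a recovery difference will be read as independent of chronicity only if it holds in the adjusted model.
5. Run a sensitivity analysis limited to participants within six weeks of episode or flare onset only if onset dates were recorded. The questionnaire is described as covering pain duration; the article does not show that flare onset was captured.

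**Cost.** No new data are needed for items 1 to 4: type is known from eligibility and pain duration from the baseline questionnaire. The price is precision in about 25 people, with a variance roughly 1.04 to 1.56 times larger depending on imbalance, and it is highest where the unadjusted contrast is least trustworthy. The adjusted contrast should therefore be labelled exploratory, and a wide interval should not be read as absence of a relation with recovery.
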